**Methods and analysis:**

To study the mechanisms by which social media and smartphone use underpin self-harm in a clinical sample of young people, the Social media, Smartphone use and Self-harm in Young People (3S-YP) study uses a prospective, observational study design. Up to 600 young people aged 13–25 years old from secondary mental health services will be recruited and followed for up to 6 months. Primary analysis will compare real-world data in the 7 days leading up to a participant or clinician recorded self-harm episode, to categorise patterns of problematic usage. Secondary analyses will explore potential mediating effects of anxiety, depression, sleep disturbance, loneliness and bullying.

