### Recruitment method and study procedures

The study team will contact eligible young people (and/or an adult with parental responsibility for young people aged 13–15 years old) by telephone, text or email to invite the young person to take part. They will be sent a unique link to the study website which will host the participant information and online consent and assent forms as well as being offered the option of a face-to-face or virtual meeting if needed. Young people aged 16–25 years old who want to take part, will be asked to confirm their consent via an online form. This will include separate consent for the following types of data collection: questionnaires, EHRs, social media and smartphone data; choosing not to consent to the latter three will not preclude participation. For young people aged 13–15 years old, an adult with parental responsibility will first be asked to confirm their consent via an online form, following which the young person will be asked to confirm their assent. A maximum of three contact attempts will be made to non-responders. The flow of participants through the study will be documented in a flowchart (see figure 1 - Participant flowchart).

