**Figure 1 F1:**
[figure not shown]
Participant flowchart.

Participants will then instal the study software application on their smartphone device and complete the baseline questionnaires. The study software application has been designed to continuously extract smartphone metadata and to deliver the questionnaires for the follow-up period (up to 6 months, reduced from 12 months following an initial pilot phase). Tables 2 and 3 outline data collection measures over the 6-month follow-up period related to primary and secondary objectives and other measurements. Participants who choose not to provide smartphone metadata (or use the study software application for any other reason) will be provided with a unique link to an online survey platform—Qualtrics (https://www.qualtrics.com)—to complete the questionnaires according to the same schedule. Participants will receive a reminder (an automated push notification and/or a prescheduled standardised text message and/or email) on the day a questionnaire is due, followed by a second reminder 7 days later if incomplete. The final set of questionnaires may also be sent via post. Participants who consent to provide their social media data will be contacted at baseline, months 3 and 6 to ask them to upload data. Participants will be given detailed guidance on how to request their data from the platforms and upload it to the study website via a unique link. Participants will receive a £10 voucher as a thank you for enrolling in the study, followed by £5 per month of continued participation and an additional £10 voucher for uploading their social media data at month 6.

**Table 2 T2:** Outline of data collection measures over the 6-month follow-up period related to primary objectives

Measure	Description	Data collected at:						
		Baseline	Month 1	Month 2	Month 3	Month 4	Month 5	Month 6
Socio-demographic questionnaire	Including age, gender, ethnicity, education and/or employment status, smoking, alcohol consumption and drug use.	X						
Child and Adolescent Self-harm in Europe (CASE) study criteria^48^	Occurrence and characteristics of historical and current (ie, in the last month) self-harm events will be collected using an adapted self-report version of the two-item CASE study criteria.^48^	X	X	X	X	X	X	X
Self-reported social media use	Including which social media platforms are used, types of activity (eg, to share something, or to comment on a post) and average duration of daily usage.	X						X

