Self-reported smartphone use	Including most frequently used apps, average duration of daily usage, and night-time access to a smartphone.	X						X
Smartphone Addiction Scale - Short Version (SAS-SV)^49^	Smartphone addiction will also be measured using the 10-item SAS-SV.^ 49 ^ Scores range between 10 and 60, with 31 and 33 representing a cut-off for smartphone addiction in adolescent boys and girls, respectively. The SAS-SV is a widely used and validated instrument which operationalises problematic smartphone usage.^50^	X				X		X
Social media data upload	Retrospective (ie, since the account was created) and prospective social media data will be uploaded by participants from their accounts on Facebook, Instagram, Snapchat, TikTok, Twitter and YouTube, including duration of usage (hours/min per day), timing of usage (diurnal/nocturnal posting), frequency of usage (visits to platforms per day), type of use and textual and imagery data.	X			X			X
Smartphone metadata extraction	Smartphone metadata will be extracted continuously for the duration of follow-up using the study software application, including intensity of usage by time of day, frequency and duration of incoming and outgoing telephone calls, frequency of incoming and outgoing text messages and length of time spent on software applications. For participants with Android phones, permissions will be set to enable the Android App Usage API to track daily statistics listed above. For iOS, low level system logs will be used to retrieve similar information as listed above, where iOS allows.	X	X	X	X	X	X	X
Electronic health records data extraction	Clinician recorded self-harm events, using a similar approach to Polling *et al,* 51 and other relevant clinical variables will be extracted from structured and free-text fields in EHR using the CRIS system. For participants who provide social media data, data will be extracted from the date of the first interaction on social media (or the date of the 13th birthday, whichever is later) to the end of the follow-up. For participants who do not provide social media data, data will be extracted from the date of the baseline assessment.	X						X

CRIS, Clinical Research Interactive Search; EHR, electronic health record.

**Table 3 T3:** Outline of data collection measures over the 6-month follow-up period related to secondary objectives and other measurements

Measure	Description	Data collected at:						
		Baseline	Month 1	Month 2	Month 3	Month 4	Month 5	Month 6

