### Outcomes, exposures and other measurements

#### Primary outcome

Participant and clinician recorded self-harm events.

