### Data analysis plan

#### Descriptive analysis

Individuals will be grouped into those that have had an episode of self-harm, and those that have not. Frequency distributions for different types of self-harm will be summarised, and individuals with multiple, versus a single episode of self-harm will be compared. Baseline sociodemographic and clinical descriptors will be presented for those that self-harm and those that do not. Patterns of social media and smartphone use will be explored using a mixed methods analysis and presented as a descriptive analysis.

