#### Primary analysis

Patterns of social media and smartphone use will be identified and categorised into specific problematic exposure groups. This will be defined using a mixed methods analysis comparing social media and smartphone data in the 7 days leading up to a self-harm episode. Individuals who do not experience an episode of self-harm will be randomly matched with four cases, and the same relative date and time of exposure will be randomly matched.

Social media and smartphone use will be compared between self-harm cases and non-cases, including social media platform of use, duration of use, time of use and absence of engagement (reduced level of posting but passive presence online). For example, night-time use compared with similar use during the day will be compared by self-harm status.

A binary generalised linear model with a log link will be fitted to derive the relative risk of a prospective self-harm episode in relation to a characteristic pattern of social media and smartphone use in the 7 days prior to the episode. Known social and physical determinants of health associated with self-harm will be included to adjust for baseline effects. Missing data will be explored for patterns of missingness. Secondary analyses will explore potential mediating effects of anxiety, depression, sleep disturbance, loneliness and bullying.

The primary analysis population under investigation will include all participants with a post-baseline assessment of self-harm.

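### Non-cases can supply matched usage windows from time when their self-harm status was not fully observed, and the binary relative-risk model carries no follow-up time

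*Protocol article*

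**What the plan says.** All references are to the protocol article.

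- **Population** (Primary analysis): it "will include all participants with a post-baseline assessment of self-harm". No number of assessments and no completeness condition is given.
- **Self-report** (Table 2, CASE row): "Occurrence and characteristics of historical and current (ie, in the last month) self-harm events will be collected", scheduled at baseline and at each of months 1 to 6.
- **Follow-up** (Abstract): participants "will be recruited and followed for up to 6 months".
- **Model** (Primary analysis): "A binary generalised linear model with a log link will be fitted to derive the relative risk of a prospective self-harm episode". No offset, person-time or censoring is mentioned.
- **Grouping** (Descriptive analysis): "Individuals will be grouped into those that have had an episode of self-harm, and those that have not".
- **Matching** (Primary analysis): non-cases are matched to cases and take an exposure window at the equivalent date and time. Nothing requires that the non-case's self-harm status was observed at that point.
- **Outcome** (Primary outcome): "Participant and clinician recorded self-harm events", so there are two sources.
- **Health records** (Table 2, last row): for participants without social media data, "data will be extracted from the date of the baseline assessment"; for those with such data, from an earlier date to the end of follow-up.
- **Consent** (Recruitment method and study procedures): for health records, social media and smartphone data, "choosing not to consent to the latter three will not preclude participation".
- **Missing data** (Primary analysis): its patterns are to be explored.

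**The concern.** Three stated choices interact: an entry rule satisfied by one follow-up assessment, an outcome whose self-reported part looks back one month, and a model that does not use observed time. A participant who answers at month 1, reports no episode and then stops enters as a non-case. The app may go on collecting phone data, so the same person can supply a comparison window in, say, month 5, when nobody asked about self-harm.

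The error is confined to non-cases. A participant with one detected episode is correctly a case however few questionnaires were returned. Some non-cases, however, will have had episodes that were never recorded. At best this removes events and power. At worst, if people with a problematic usage pattern respond less often (or more often) than others, it distorts the relative risk, and the direction cannot be recovered afterwards from the ever/never data. Such a link is plausible because the exposure is phone and social media behaviour and the questionnaires are delivered mainly through a phone app, but the document gives no figure for it.

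**Working it through.** **Step 1. Follow one participant through the rules.** Month 1 is answered with no episode; months 2 to 6 are unanswered; no episode is recorded.

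- Entry: yes, one post-baseline assessment exists.
- Status: no recorded episode, hence a non-case.
- Self-report coverage: 1 of 6 months.
- Health-record coverage: clinician-recorded events in months 2 to 6 if the participant consented to record access, none otherwise.
- Control window: any matched date with usage data, including months 2 to 6.

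**Step 2. Reproduce the plan's own figure.** Inputs from Sample size calculation: risks 22.5% and 35%, 480 followed up, 5% significance. Assumed, because not stated: two-sided, equal exposure groups of 240.

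- Pooled risk 0.2875; null SE = √(0.2875 × 0.7125 × 2/240) = 0.0413
- Alternative SE = √((0.225 × 0.775 + 0.35 × 0.65)/240) = 0.0409
- Power = Φ((0.125 − 1.96 × 0.0413)/0.0409) = 85.9%, against the stated 86%

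The figure reproduces. It gives all 480 the full risk. The entry rule does not require full follow-up: any of the other 600 − 480 = 120 with one follow-up assessment would also enter.

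**Step 3. Risk visible when only m of 6 months are observed.** Assume a constant monthly hazard and no record capture: p(m) = 1 − (1 − p)^(m/6).

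- m = 1: 1 − 0.775^(1/6) = 4.2% instead of 22.5%; 1 − 0.65^(1/6) = 6.9% instead of 35%
- m = 3: 12.0% and 19.4%

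**Step 4. A share f of participants is partly observed.** Observed risk = (1 − f) × p + f × p(m). Both f and m are assumptions.

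Same f in both exposure groups (true relative risk 0.35/0.225 = 1.56):

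| f | RR, m = 1 | Power, m = 1 | RR, m = 3 | Power, m = 3 |
|---|---|---|---|---|
| 10% | 1.56 | 82% | 1.56 | 84% |
| 20% | 1.56 | 77% | 1.56 | 82% |
| 30% | 1.56 | 72% | 1.57 | 80% |
| 50% | 1.57 | 60% | 1.58 | 75% |

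Worked line, f = 20%, m = 1: unexposed 0.8 × 0.225 + 0.2 × 0.0416 = 0.1883; exposed 0.8 × 0.35 + 0.2 × 0.0693 = 0.2939; ratio 1.56. Expected events fall from 240 × (0.225 + 0.35) = 138 to 240 × (0.1883 + 0.2939) = 116.

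Different f by exposure:

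| f exposed / f unexposed | True RR | RR, m = 1 | RR, m = 3 |
|---|---|---|---|
| 40% / 20% | 1.56 | 0.2377/0.1883 = 1.26 | 0.2875/0.2039 = 1.41 |
| 20% / 40% | 1.56 | 0.2939/0.1516 = 1.94 | 0.3188/0.1829 = 1.74 |
| 40% / 20% | 1.00 (both 28.75%) | 0.81 | 0.90 |
| 20% / 40% | 1.00 (both 28.75%) | 1.24 | 1.11 |

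**Step 5. What this leaves out.** It is a fixed-exposure cohort comparison, not the matched 7-day-window design, and it gives health records no credit. It shows direction and sensitivity, not a forecast.

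**The case against.** The strongest reply is that nowhere does the article say an unobserved month is coded as free of self-harm. The ever/never split stands under Descriptive analysis, and rules on partial follow-up, censoring and eligible control dates may sit in the full protocol or an analysis plan that is not shown. That is right about the missing-data detail. It does not dispose of the point, which rests on what the article does fix: the entry rule, the binary model and the date matching. Followed as written, these give the result in Step 1.

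Four further points stand and limit the size:

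- The outcome has a second source. For participants who consent to record access, unanswered months are still covered for clinician-recorded events. Cover is partial, because consent is optional and the Introduction itself notes that young people are often reluctant to disclose and seek help.
- The CASE item also covers historical events, so a later answer might recover a skipped month. It cannot do so after permanent dropout.
- A non-case with no usage data in the matched window has no exposure to classify and would drop out as missing. The problem is confined to windows with usage data but no self-harm assessment.
- The article allows for loss from 600 to 480, plans reminders and possible postal delivery of the last questionnaires, and lists missing data as a limitation.

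A reader might go further and infer that every unanswered month is wholly unobserved, or that the relative risk is bound to be biased. The documents support neither: clinician records fill part of the gap, and with equal coverage the relative risk hardly moves.

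**Conclusion.** The point holds as a defect in how comparison time is chosen, and it should be put right before the analysis. A participant without a recorded episode who stops responding is treated as a non-case for time when self-harm was not fully observed.

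The certain cost is lost events and power: from 86% down to between 60% and 84% across the equal-coverage scenarios. Bias in the relative risk is conditional on response differing by usage pattern. With the assumed 40%/20% splits at one observed month, a true 1.56 would read anywhere from 1.26 to 1.94, and a true 1.00 from 0.81 to 1.24; at three observed months the ranges narrow to 1.41 to 1.74 and 0.90 to 1.11. All these figures assume a constant hazard, the stated shares and months, equal exposure groups where power is quoted, and no health-record capture. Record capture would reduce them by an amount the article does not allow one to estimate.

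**What to change.** - Define each participant's observed period as the months covered by a completed CASE questionnaire.
- Draw non-case windows only from observed time in which usage data exist.
- Keep all participant- and clinician-recorded episodes as cases, as the primary outcome states, including clinician-recorded episodes in months with no questionnaire.
- As a sensitivity analysis, treat months covered only by the health record as observed among participants who consented to record access. This also tests the asymmetry left by the main rule, under which a case can arise in a record-only month but a control window cannot. Alternatively, fit a person-month model with a log link, so that the estimate remains a relative risk.

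The cost is plan wording and minor programming on data already being collected. Some non-case time leaves the analysis, and the approach still assumes that non-response is unrelated to self-harm given the covariates; that assumption should be stated.

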#### Natural language processing and language analysis

In previous work by coauthor [name]’s team^30^ aggregates of both language and smartphone features were obtained at hourly intervals preceding an episode (administration of a mood form). These were used in linear and non-linear regression models for prediction of mood scores. Recent work by [name]’s team has developed natural language processing methods to identify changes in the mood of individuals over time through sequential analysis of 2-week user timelines on social media,^31^ and has shown that capturing such changes can be predictive of suicidality risk.^32^ The current protocol focuses on the 7-day window preceding a self-harm episode, making the above-mentioned research directly applicable to this work. While language features used in earlier work includes word embeddings (sentiment specific and others), n-grams, topics and lexica for sentiment, recent developments have shown the success of pretrained language models (eg, BERT from Devlin *et al*)^33^ in capturing information on mental health.^31 34^ The textual content of individuals posts will be represented using pretrained language models, combined with other smartphone data, to predict both moments of change and episodes of self-harm. Our earlier work on fusing heterogeneous features using multiple kernel learning,^30^ will provide useful baselines. Measurements of affective change both through our models for moments of change^31^ as well as more traditional measures of valence and affect^35^ will feed into the predictive models as well as the descriptive analysis. Models will be evaluated under robust cross validation settings to simulate as much as possible a real-world scenario and avoid overfitting.^36^

#### Qualitative analysis

Thematic analysis,^37^ which has been successfully applied in the analysis of social media data of patients and self-harm online communities,^38 39^ will be employed to explore characteristic patterns of social media use in the 7 days leading up to a self-harm episode from a qualitative perspective, complimentary to the main analyses. Thematic analysis comprises six stages: (1) familiarisation with the data; (2) generation of initial codes; (3) development of themes; (4) review of themes; and (5) defining themes; and (6) writing up the findings.^37^

Data from a purposive sample of cases will be selected for this analysis, based on age, sex, ethnicity, frequency of social media usage around the time of a self-harm episode and type of self-harm behaviour. Consistent with related work in this field (eg, Williams *et al*)^38 39^ around 500–600 social media postings will be analysed. Following removal of any personally identifiable/geographical material and duplicate material (for example, retweets on Twitter), the textual and imagery data of social media posts in the 7 days leading up to and including an episode of self-harm will be analysed using inductive and deductive methods to validate and refine the emerging themes.^40^ Inductive methods comprise repeated reading of the data to identify salient themes and deductive methods involve testing out predefined themes based on the research question and existing theories, for example, cry of pain theory/integrated motivational-volitional model.^41 42^ Analysis of visual data will include descriptive summaries of the visual content as well as analysis of thematic content. Coding frames for the analysis of textual and visual data will be developed by the study team, informed by relevant published literature (eg, Shanahan *et al*)^39^ the research question and predefined themes. The coding frames will be refined deductively throughout the analytical process.

### Process evaluation

Data from participant contact will be collected by the study team to evaluate the study processes for acceptability, feasibility and value. Reasons for decline and withdrawal will be coded and categorised where appropriate and summarised using descriptive statistics. A purposive sample of up to 20 participants (who provided consent to be contacted for further research when they enrolled in the 3S-YP study) will be invited to take part in a brief telephone or in person interview. Participants will complete a separate consent form and interviews will take place following study completion or drop out from the study (including participants who withdraw or stop providing data to the study). Interviews will be audio recorded and transcribed verbatim. Participants will receive a £20 voucher as a thank you for taking part. Interview data will be analysed using Braun and Clark’s^37^ thematic analysis approach, as outlined above.

Data will be handled in accordance with the General Medical Council guidance on confidentiality,^45^ the principles of Good Clinical Practice, European General Data Protection Regulations^46^ and UK Data Protection Act.^47^

### Dissemination plan

Data collected in the study will not be made publicly available as it is not possible to guarantee that an individual could not be identified as a participant from their publicly available social media data. The findings will be disseminated through peer-reviewed scientific journals, conferences, websites, social media and stakeholder engagement activities.

### Project oversight

Project oversight is provided by our steering group, comprised of researchers and clinicians from across the fields of self-harm and suicide prevention, Child and Adolescent Mental Health Services(CAMHS), data science, public health, sleep medicine, cyberbullying and addictions, as well as young people with lived experience, representatives from the leading national UK youth mental health charity—YoungMinds, and communications and funding advisors. The group will meet at regular intervals throughout the study. The role of the group is to monitor study conduct and progress and contribute to decision-making and solution generation. The group will not have access to participants’ personal data.

